## Abstract

**Background:**

Helping trainees develop appropriate clinical reasoning abilities is a challenging goal in an environment where clinical situations are marked by high levels of complexity and unpredictability. The benefit of simulation-based education to assess clinical reasoning skills has rarely been reported. More specifically, it is unclear if clinical reasoning is better acquired if the instructor's input occurs entirely after or is integrated during the scenario. Based on educational principles of the dual-process theory of clinical reasoning, a new simulation approach called simulation with iterative discussions (SID) is introduced. The instructor interrupts the flow of the scenario at three key moments of the reasoning process (data gathering, integration, and confirmation). After each stop, the scenario is continued where it was interrupted. Finally, a brief general debriefing ends the session. System-1 process of clinical reasoning is assessed by verbalization during management of the case, and System-2 during the iterative discussions without providing feedback.

**Objective:**

The aim of this study is to evaluate the effectiveness of Simulation with Iterative Discussions versus the classical approach of simulation in developing reasoning skills of General Pediatrics and Neonatal-Perinatal Medicine residents.

**Methods:**

This will be a prospective exploratory, randomized study conducted at Sainte-Justine hospital in Montreal, Qc, between January and March 2016. All post-graduate year (PGY) 1 to 6 residents will be invited to complete one SID or classical simulation 30 minutes audio video-recorded complex high-fidelity simulations covering a similar neonatology topic. Pre- and post-simulation questionnaires will be completed and a semistructured interview will be conducted after each simulation. Data analyses will use SPSS and NVivo softwares.

**Results:**

This study is in its preliminary stages and the results are expected to be made available by April, 2016.

**Conclusions:**

This will be the first study to explore a new simulation approach designed to enhance clinical reasoning. By assessing more closely reasoning processes throughout a simulation session, we believe that Simulation with Iterative Discussions will be an interesting and more effective approach for students. The findings of the study will benefit medical educators, education programs, and medical students.

## Introduction

### Background

#### The Importance of Clinical Reasoning in Medicine

Diagnostic errors account for more than 8% of adverse events in medicine and up to 30% of malpractice claims [1]. These errors may be related to the working environment but clinical reasoning issues are involved in about 75% of the cases, either alone or in association with system failures [2].

In this context, clinical reasoning is a crucial skill for all physicians regardless of their area of expertise and becomes a central aim of medical education [3]. The clinical reasoning process is largely supported by several decades of research in cognitive psychology and has been extensively published [4-6]. The most accepted model of clinical reasoning is called *dual-process framework* and consists of two independent systems [7]. System-1 is automatic, intuitive, nonanalytical, and error-prone. It leads to the immediate recognition of the clinical constellation and the generation of a working diagnostic hypothesis. System-2 is slower, more analytical, and conscious [8,9]. Novices employ this analytic mode of reasoning more frequently than their experienced counterparts because they lack the necessary experience for System-1 reasoning. Dual-process theory posits that both systems are simultaneously required in most clinical scenarios and has been associated with better diagnostic outcomes [10]. However, in what situations does the valence go towards one system or another remains unclear and how both systems are activated and used is still under study and debated [11-13]. Preliminary conclusions from recent publications describe that the analytical system is primarily used in the following situations [14,15]: when time permits, when there are high-stakes outcomes, when the situation is complex, when the decision-maker is facing ambiguous, nonroutine or ill-defined problems, and in the context of uncertainty. In contrast, routine problems associated with a higher level of certainty would be more often dealt with by the intuitive system, especially when time is lacking [11-13].

Another challenge for medical educators is the assessment of residents’ clinical reasoning [3]. Because of the paucity of scientific evidence about optimal evaluation, both quantitative and qualitative clinical reasoning assessment tools have been reported [5,16-19]. However, the following general issues arise from these tools: (1) diagnostic reasoning must be inferred from behavior because it is not a discrete and measurable quality; (2) most of these instruments are performed in the classroom that emphasize the assessment of System-2, but not System-1 reasoning nor the shift between automatic and analytic reasoning [15,16]; and (3) rater’s personal knowledge, experience, ability, and cognitive biases influence his or her adjudication of a learner’s performance in a nonstandard fashion [20-24]. Moreover, reasoning assessment can be highly complex and dependent upon the context. Durning et al [25] have recently reported the influence of three environmental factors on clinical reasoning: (1) the patient’s specific problem (patient factors); (2) the setting in which the patient is evaluated (encounter factors) [10,26]; and (3) human-factors such as fatigue, well-being, and sleepiness (doctor factors). They emphasize the importance of measuring the environment as a part of the signal, rather than part of the “noise”, which is to be minimized and generally ignored [27-29].

#### Simulation-Based Education as a Strategy to Enhance Clinical Reasoning Skill

Simulation-based education (SBE) has recently emerged as an instrument with potential to assess diagnostic reasoning [16,30,31]. Based on Kolb’s learning cycle [32], true learning is depicted as a four-part process in a cycle. Individuals learn through concrete experience (phase 1), reflection on the experience (phase 2), conceptualization of their reflective observations into more abstract models (phase 3), and experimentation of these new principles and conclusions to guide subsequent decisions and actions that lead to new concrete experiences (phase 4). Phase 2 and phase 3 are components of debriefing, a learning activity that generally follows a simulation experience. According to many authors, debriefing could provide an opportunity for residents and faculty to re-examine what occurred during the simulation process and detect possible flows in the reasoning process [33-45].

An important question remains whether exploration of the diagnostic process, by providing an opportunity for learners to reflect upon past clinical decisions, is more effective after the scenario or if it is integrated during the simulation session [45,46]. In the classical approach of simulation, debriefing follows the simulation experience. However, the educational valence of this type of session presents several limitations concerning the clinical reasoning assessment. First, this way of *reflection-on-action* means that it is mainly the analytical part of the reasoning process that is explored during the debriefing, without focusing on the intuitive process [47]. Second, after a stressful scenario, residents frequently forget or modify what they said or thought according to the evolution of the case, even if video recordings provide insight into what may not be documented in the medical record or fully observed in real time [45].

We believe that changes in the organization of a simulation session could allow better assessment of both System-1 and 2 of the reasoning process. First, *reflection-in-action* should be encouraged by concurrent verbalization to let the tutors know about the student’s intuitive System-1 thinking during management of a patient [11-13]. Second, *reflection-on-action,* which reflects analytical System-2 should be encouraged by in-simulation interruptions at key moments of the clinical reasoning process [48,49]. These interruptions could be assimilated to a dynamic and decision-dense environment where clinical reasoning constructs must be considered, as studies suggest that the average time on particular tasks is limited to less than 2 minutes, and interruptions occur every 2 to 10 minutes in the emergency department [50-52]. Finally, the active experimentation of newly acquired conceptualizations in a subsequent part of the scenario may avoid the learner’s return to actions based on habits and nonreflective experience [32]. Based on these arguments, we present a new approach of SBE, called simulation with iterative discussions (SID). The simulation session is designed as a single scenario with a computerized mannequin where the instructor interrupts the flow of the scenario at three key moments to cue residents towards the appropriate medical management of the case. The objectives of the session are to build a scaffold of clinical reasoning competencies throughout the scenario while continuing to manage the patient, and to improve concept acquisition and retention with spaced learning. We believe that a closer assessment of both System-1 (by concurrent verbalization during patient management) and System-2 (during iterative discussions) will improve students’ capability to self-improve clinical reasoning skills in an authentic setting.

#### Why Is It Applied in Neonatology?

Implementing a new educational strategy that assesses clinical reasoning should be particularly exciting in a busy clinical environment such as neonatology. In contrast to the well-established management of neonatal emergencies at birth [53], most daily clinical situations managed in neonatology are nonroutine or ill-defined problems marked by high levels of complexity and unpredictability, requiring that clinical reasoning is solely based on the analytical System-2 [3,6,14,15,54]. Moreover, the frequency and the impact of diagnostic errors and cognitive biases increase in emergency settings due to several factors such as stress, fatigue, circadian disruptions, time constraint, and noisy environment. In these high-risk situations, physicians rely on System-1 process [55-58]. By enabling both System-1 and 2 of clinical reasoning, practicing neonatology requires robust clinical reasoning abilities in addition to cognitive, technical, and behavioral skills.

### Aim of the Study and Working Hypotheses

The aim of this study is to explore how clinical reasoning abilities of residents in General Pediatrics and Neonatal-Perinatal Medicine evolve and are learned with the SID in comparison to the classical approach of simulation.

We hypothesize that (1) SID allows better assessment of both System-1 and 2 of clinical reasoning; (2) SID promotes higher self-progression of the clinical reasoning process when compared to the classical approach of simulation; (3) concurrent verbalization benefits mainly novice residents with underdeveloped System-1 reasoning process; and (4) iterative discussions benefit both novice and expert residents by enhancing System-2 processes.

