### Study Design

This is a prospective exploratory nonblinded randomized mixed-methods study. Both quantitative and qualitative research methods will be used simultaneously as to comprehensively explore how clinical reasoning develops through both simulation modalities.

Randomization will be stratified according to two different groups depending on their level of exposure to the NICU: (1) novice residents (PGY1 and 2, exposed to less than 8 weeks to the NICU), and (2) expert residents (PGY3-6, exposed to at least 8 weeks to the NICU). These residents have been respectively exposed to at least 5 or 15 simulation sessions during their residency training. Residents will be randomly (by draw of names) allocated by the primary investigator to group A or group B (Figure 1). Group A will be exposed to the SID approach, whereas group B will be exposed to the classical approach of simulation. Participants will be scheduled to complete the study protocol in 60 minutes. In the first 5 minutes, participants will complete the presimulation questionnaire and receive a brief introduction including a period to get physically familiarized with the mannequin (SimNewB; Stavanger, Norway). In the next 30 minutes, residents will complete the clinical simulation scenario after reading a clinical vignette. At the end of the session, participants will have 5 minutes to complete the postsimulation questionnaire (see Multimedia Appendix 1). The course will end with a 20 minutes semistructured interview.

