#### Description of the Intervention

The SID approach (Figure 2a) consists of a scenario interrupted at three moments and followed by a short debriefing. According to Kuhn’s steps of the medical reasoning process [60], the session is divided into “data gathering”, “data integration,” and “data confirmation”. Each part consists of two phases. First, the participant is asked to manage a simulated patient based on a real-life and complex case. Complexity, uncertainty and environmental factors such as doctor, patients, and encounter factors [25] are voluntarily embedded. The participant is also asked to verbalize his or her first *intuitive* diagnosis as it comes in mind by System-1 activation. Second, the scenario stops and the instructor questions the participant on his clinical reasoning process at that point in time by System-2 activation. Each interruption must be as short as possible in order to keep the trainee in action, and is ended by a one-sentence reconceptualization of the scenario by the instructor before pursuing the scenario (for the two first stops). Discussions include questions regarding data gathering and the rationale of ordered investigations (first stop), data integration, and how investigation results helped reach a diagnosis (second stop), and finally data confirmation and how the management decisions were reached (third stop). There is neither feedback nor guidance from the instructor during the stops in order to not interfere with the participant’s ongoing clinical reasoning process. These stops are “discussions” and not “debriefings”. A short general debriefing ends the session, and provides feedback on reasoning, procedural skills, and knowledge by highlighting the learnt key messages.

The classical approach (Figure 2b) consists of a scenario with no intervention provided by the instructor until debriefing. As in the SID approach, the participant must verbalize his reasoning process and the diagnostic hypotheses as they come to mind during the scenario. Immediately after the scenario, a facilitated debriefing is performed. This debriefing lasts two to three times the length of the scenario and focuses on the participant’s clinical reasoning skills.

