#### In-Simulation Clinical Reasoning Assessment

In constructing the simulation scenario and vignette, defined cues will be embedded to stimulate hypothesis generation using System-1 of clinical reasoning. After reading the initial patient presentation in the vignette, residents are asked to submit their diagnostic hypothesis by writing. Then, during the scenario, the participant’s verbalization (which is also stimulated by given cues from the nurse) of diagnosis coming to mind will be audio recorded. Both the written and audio-recorded hypotheses will be compared to the diagnoses generated by an expert panel that will be submitted to the same scenario. For example, the presence of thrombocytopenia during the data confirmation part should lead to verbalization of (1) bacterial infection, (2) viral infection, (3) intrauterine grown retardation, and (4) platelets immunization. The presence of skin lesions during the data confirmation part should lead to verbalization of (1) herpetic infection, (2) bacterial infection, and (3) varicella infection.

Iterative discussions supported by the Clinical Reasoning Assessment Tool during SID have been designed to allow development and exploration of System-2 of clinical reasoning regarding data collection, diagnostic hypotheses generation, new data interpretation, and management plan. In the classical approach, it is hypothesized that System-2 is discussed during the debriefing period after the simulation. Exploration of how both simulation approaches impact on performance of System-2 will be done during the semistructured interviews (see below).

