## Discussion

Clinical reasoning is an essential skill for everyday medical practice. However, many questions remain regarding how efficiency of the reasoning processes can be most accurately measured [16]. We believe that medical simulation could represent an effective environment for clinical reasoning assessment, as participants are immersed in an authentic and controlled setting [70]. Moreover, SID, an innovative approach to simulation, could provide a closer assessment of both System-1 and 2 of clinical reasoning by the combination of concurrent verbalization and iterative discussions at key steps of the reasoning process.

In this exploratory randomized study, comparing SID to the classical approach of simulation, we expect to find a higher progression of residents’ self-assessed clinical reasoning process with SID. More precisely, iterative discussions, by allowing reflection, will lead to improvement in System-2 clinical reasoning process while concurrent verbalization during management of the mannequin will enhance performance of System-1. Verbalization during the classical approach will also have a similar impact on System-1 clinical reasoning. Finally, residents will demonstrate a higher level of satisfaction in the SID approach of SBE.

This is the first randomized study comparing a new simulation approach to the classical mode for developing clinical reasoning skills. In addition, incorporating a qualitative piece to the study with the goal of exploring how each simulation approach impacts on residents’ clinical reasoning process is of great interest. Residents of different training levels are included in the study allowing to explore the phenomenon from perspectives of individuals with various levels of clinical reasoning performances. There are also a few limitations to the study. The small sample size does not allow for statistical generalizability of quantitative results. The absence of a robust pre and post assessment of residents’ clinical reasoning abilities might not portray the exact impact of each intervention. However, in the absence of a gold-standard tool in clinical reasoning evaluation, this exploratory study could provide detailed and useful preliminary data for the effectiveness of such a new simulation approach. Finally, the case specificity of one unique scenario could limit generalizability of the results.

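### Hypothesis 3 (verbalizing helps mainly novices) cannot be tested as an effect of verbalization, because every resident in both arms verbalizes

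*Protocol article*

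**What the plan says.** The Aim of the Study and Working Hypotheses section of the protocol article lists four hypotheses. The third is that "concurrent verbalization benefits mainly novice residents with underdeveloped System-1 reasoning process".

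Study Design gives two arms and no others: "Group A will be exposed to the SID approach, whereas group B will be exposed to the classical approach of simulation". Training level enters as a stratification factor: "Randomization will be stratified according to two different groups depending on their level of exposure to the NICU". The abstract's Methods state that residents "will be invited to complete one SID or classical simulation", that is, one session each.

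Description of the Intervention then covers verbalization arm by arm. For SID: "The participant is also asked to verbalize his or her first" intuitive diagnosis. For the classical arm: "As in the SID approach, the participant must verbalize his reasoning process and the diagnostic hypotheses as they come to mind during the scenario".

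In-Simulation Clinical Reasoning Assessment describes the System-1 measure without distinguishing the arms: "Both the written and audio-recorded hypotheses will be compared to the diagnoses generated by an expert panel".

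The Discussion first explains the expected SID advantage partly by verbalization improving System-1. It then adds, of the comparator: "Verbalization during the classical approach will also have a similar impact on System-1 clinical reasoning".

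**The concern.** Hypothesis 3 says that a component of the session has a benefit and that the benefit depends on training level. To examine it as an effect, some residents, or some sessions, must lack that component. None do. What the randomization varies is the stops with iterative discussions and the kind and length of debriefing, not whether residents talk aloud.

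The risk lies in the reporting. Novices and experts will very probably differ, since Setting and Population itself says that reasoning ability improves from the first to the sixth year of residency. With hypothesis 3 on the list, such a difference could be read as evidence for or against a benefit of verbalizing. Data Analysis says that the study will help to plan a larger randomized trial, so an unsupported conclusion could be carried into that design.

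**Working it through.** No sample size, power or error rate in the protocol is tied to hypothesis 3, so there is no figure to reproduce. The check is whether the quantity can be identified from the design.

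**Inputs**
- Arm A: SID or classical (Study Design).
- Stratum S: novice (PGY1 and 2) or expert (PGY3 to 6), not randomized (Study Design).
- Verbalization V: 1 in SID and 1 in classical (Description of the Intervention).
- Sessions per resident: one (abstract, Methods).

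**Step 1. What hypothesis 3 asks.** Write m(V, S) for the mean System-1 result. Hypothesis 3 concerns

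[m(1, novice) − m(0, novice)] − [m(1, expert) − m(0, expert)] > 0.

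Both m(0, ·) terms describe residents who do not verbalize. The design has none.

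**Step 2. What the design can estimate.** There are 2 arms × 2 strata = 4 cells, which support four parameters: intercept, A, S and A×S. Because V = 1 for everyone, the V column equals the intercept, V×S equals S, and V×A equals A. Adding verbalization therefore adds no estimable term.

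**Step 3. The contrast between arms.** Exposure to verbalization, SID minus classical:
- novices: 1 − 1 = 0
- experts: 1 − 1 = 0

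This does not change with sample size. It holds at the 20 to 25 residents at which saturation is expected and equally at the approximately 50 in the target population.

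**Step 4. Whether another comparison can stand in.**
- *A×S.* This asks whether the whole SID package (stops and discussions with a short debriefing, against an uninterrupted scenario with a long debriefing) works differently in novices and experts. It carries no verbalization contrast.
- *S alone.* This compares novices with experts, all of whom verbalize. It contains whatever years of training contribute.
- *Written against verbalized hypotheses.* The written ones follow the vignette. The verbalized ones come during the scenario, after new findings and with prompts from the nurse. A change between them mixes speaking aloud with added information.
- *Pre- and post-session questionnaires.* Self-rated change covers the whole session, including debriefing.
- *Difference in instruction.* SID residents are asked for a first intuitive diagnosis; classical residents for their reasoning and hypotheses. That is a variation in wording, not presence against absence, and the Discussion expects a similar System-1 impact.

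**Step 5. The two Discussion statements side by side.** One offers verbalization as the route by which SID improves System-1. The next expects much the same from the classical arm. Together they leave no System-1 gain specific to SID that could be attributed to verbalization.

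**The case against.** The strongest reply is that the study is declared exploratory and mixed-methods, that these are working hypotheses, and that hypothesis 3 is not worded as a comparison of arms; only hypothesis 2 names the classical approach. The authors also foresee a similar System-1 effect in both arms, so they do not claim a verbalization advantage for SID over classical. The interviews, the questionnaires and the written and spoken hypotheses will all give information by training level.

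Much of this stands. The information is not empty: it can describe how novices and experts verbalize and how they perceive it. The defect changes neither allocation nor data collection. But an exploratory label weakens the strength of inference; it does not supply a missing comparator. The hypothesis is worded as a benefit, and the limitations in the Discussion (small sample, no robust pre and post assessment, one scenario) do not mention this one.

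A reader might infer more than the protocol supports:
- *That the System-1 part of hypothesis 1 falls as well.* It does not. Hypothesis 1 is about better assessment, not learner benefit, and Data Analysis assigns that question to the qualitative data. It can be examined with both arms verbalizing.
- *That hypothesis 4 lacks an analysis by stratum.* The article is condensed and the analysis plan is not shown, so this absence is no finding. An arm-by-stratum term would in any case test the whole SID package rather than the discussions alone.
- *That the strata are too small.* Precision depends on whether recruitment stops at 20 to 25 or takes in about 50, and on how the strata split. It has no bearing on hypothesis 3, for which the contrast is zero at any size.

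**Conclusion.** The point holds for hypothesis 3 only. Neither an effect of concurrent verbalization nor its interaction with training level is identifiable: the contrast is exactly zero in both strata, whatever the sample size, and no analysis plan could repair that. It affects one of four working hypotheses and leaves the SID-versus-classical comparison intact.

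The conclusion rests on three statements in the article: residents in both arms verbalize, there are only two arms, and each resident completes one session. It also assumes that the sessions are run as described. Incidental differences in how much residents actually talk would not be randomized and could not serve as a comparator.

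**What to change.** 1. Restate hypothesis 3 as a descriptive and qualitative question: how novices and experts differ in their written and verbalized hypotheses and in their interview accounts of verbalizing, pooled over both arms, with no causal claim for verbalization.
2. In the Discussion, reconcile the expectation that verbalization will enhance System-1 with the statement that the classical arm will have a similar impact, so that no System-1 gain specific to SID is attributed to verbalization.
3. Add to the limitations that there is no comparator without verbalization. If its effect matters, the planned larger trial could include one, for example in a factorial design.

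Hypothesis 1 stays as it is. The cost is wording only: no new data, no change to randomization or sessions. The price is that hypothesis 3 is given up as a statement about an effect.
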